### Previous work comparing UAE with myomectomy

The use of UAE in women who may wish to conceive is controversial within some sections of the medical community. Some authors are concerned by the reduction in blood flow to the ovary that can occur if there are significant connections between the ovarian and uterine arteries, which may result in decreased ovarian function [5]. The extent of this decreased function, how long it is maintained for, and even if it occurs at all, is disputed [6, 7]. Whilst generally regarded as safe [8], the caution inherent in the guidelines drawn up when UAE was still in its infancy has led to a further reluctance in some circles to use UAE in women who may wish to try to conceive at some point. As a result of this, trials generally excluded women who are seeking fertility.

One small (n = 121) single centre, randomised, clinical trial from the Czech Republic compared myomectomy with UAE in women with intramural fibroids [9]. These authors concluded that UAE was less invasive, but as effective and safe as myomectomy for treating the symptoms of fibroids. The REST trial [10] randomised a total of 157 women in a 2:1 ratio between UAE and myomectomy before assessing the quality of life (QoL) at five years with the Short Form 36 (SF-36) general health survey. Secondary measures included complications, adverse events, and the need for further intervention. These authors reported that there were no significant differences in the reported QoL between the groups at five years. However, there was a significantly greater re-intervention rate after five years for treatment failure or complications in the UAE arm over the myomectomy arm. This negated the initial cost benefit of UAE over surgery at 12 months and made both treatments cost-neutral at five years [10].

A pilot study for the FEMME trial (the FUME study [11]) was conducted at St George’s Hospital, London, United Kingdom. In this study 160 women with symptomatic uterine fibroids were randomised to UAE or myomectomy and the change in their QoL, hospital stay, complication rates, and need for re-intervention were measured at one year post-procedure. The authors reported that by one year there was no difference in the improvement of the QoL women experienced in the myomectomy and UAE arm but, like the REST trial, there was a higher intervention rate in women who had undergone a UAE [11].

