### Treatment

A pregnancy test will be performed immediately prior to treatment. As FEMME is a pragmatic trial, other than the randomisation to myomectomy or UAE the treatment the woman receives is the clinician’s normal practice. This means that if the woman is randomised to a myomectomy this can be of any type including laparoscopic, hysteroscopic, or by a laparotomy. Similarly, should the woman be randomised to UAE, this is performed according to the interventional radiologist’s normal practice. Information collected at the time of the procedure will include details of the treatment received, any adverse events experienced by the participant, and the length of in-patient stay.

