#### Primary and interim analysis

HRQL scores from the UFS-QoL will be analysed using a linear model (analysis of covariance) with estimates of difference between groups adjusting for the baseline score. Results of the primary outcome score at other time-points, along with the results of other continuous-type measurements (for example, symptom severity score from the UFS-QoL questionnaire, EQ-5D and Blood Loss scores) will be analysed in a similar fashion. Further analysis of continuous measures will be undertaken using a repeated measure multilevel model to examine any differential effect over time [12].

Dichotomous measures (for example, pregnancy or re-intervention rates) will be analysed using relative risks and chi-squared tests at each time-point. Variables, including pregnancy and any re-intervention, will also be explored using standard time-to-event analysis methods (log-rank test). All analyses will be performed using the intention-to-treat principle, with effect sizes presented as point estimates and corresponding 95% confidence intervals. A more comprehensive analysis plan will be made available for review by the Data Monitoring Committee (DMC).

An interim report, including the analysis of major endpoints, will be provided in strict confidence to the Data Monitoring and Ethics Committee at intervals of at least 12 months, or as requested by the DMC.

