#### Handling missing data

In the first instance analysis will be completed on received data, with every effort made to follow-up participants (even after protocol treatment violation) to minimise any potential bias. Sensitivity analysis of the primary outcome measure, including imputed values for missing responses, will be performed to determine the robustness of the results obtained. Methods based on multiple imputation will be used.

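### All analyses, including ovarian reserve and procedure-related adverse events, follow intention-to-treat; no supplementary analysis by procedure received is stated for these harm questions

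*Protocol article*

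**What the plan says.** The section Primary and interim analysis of the protocol article gives one rule for all outcomes: "All analyses will be performed using the intention-to-treat principle". It makes no exception. The section Secondary outcomes lists AMH, compared at six weeks, six months and twelve months after the procedure, and adverse events judged related to the protocol or the intervention. Both therefore fall under the rule.

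Three other sections bear on the point:

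- Handling missing data provides for analysis of the data received, "with every effort made to follow-up participants (even after protocol treatment violation) to minimise any potential bias". The only sensitivity analysis named there concerns missing responses: "Sensitivity analysis of the primary outcome measure, including imputed values for missing responses, will be performed to determine the robustness of the results obtained".
- Treatment says: "Information collected at the time of the procedure will include details of the treatment received".
- Previous work comparing UAE with myomectomy explains why ovarian reserve is studied: embolisation may reduce blood flow to the ovary, "which may result in decreased ovarian function".

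The article names no as-treated, per-protocol or adherence-adjusted analysis. It refers to a fuller analysis plan for review by the Data Monitoring Committee, which is not shown.

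**The concern.** The quality-of-life question is one of treatment policy: what follows from allocating a woman to UAE or to myomectomy. Analysis by allocation answers it. The ovarian-reserve question, as the article's background frames it, is about a biological effect of embolisation. A woman allocated to UAE who is never embolised cannot show that effect, yet she counts in the UAE group. Likewise, a complication caused by a myomectomy in a woman allocated to UAE is counted against UAE.

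The background section calls the extent, duration and even the existence of an ovarian effect disputed, and describes reluctance to use UAE in women who may wish to conceive. If the only estimate reported is by allocation, a finding of similar AMH or similar complications could partly reflect women who did not have their allocated procedure.

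**Working it through.** **What the documents supply.** They give no rate of non-receipt. The section Sample size makes allowances for pregnancy (10% or less) and loss to follow-up (10%) only: 172 / (1 − 0.20) = 215, or 216 as an even number, which reproduces the stated target. It contains no allowance for switching. All rates below are therefore assumptions.

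**Swaps to the other procedure.** Let μ_U and μ_M be the mean outcomes under UAE and myomectomy, and let c_UAE and c_myo be the shares of each arm that have the other procedure. Assume that swappers respond like the average woman.

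- Mean in the UAE arm: (1 − c_UAE) μ_U + c_UAE μ_M
- Mean in the myomectomy arm: (1 − c_myo) μ_M + c_myo μ_U
- Difference by allocation: (1 − c_UAE − c_myo) × (μ_U − μ_M)

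| Swap in each arm (assumed) | Share of the true difference kept |
|---|---|
| 5% | 90% |
| 10% | 80% |
| 15% | 70% |
| 20% | 60% |

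With swaps in one arm only, the share kept is 1 − c.

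**Women who have neither procedure.** The formula does not cover them. Take adverse-event risks, all assumed, of 30% with myomectomy, 20% with UAE and 2% with neither, so that the true difference is 10 points.

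| Departure (assumed) | Myomectomy arm | UAE arm | Difference |
|---|---|---|---|
| None | 30% | 20% | 10.0 points |
| 10% swap in each arm | 0.9 × 30 + 0.1 × 20 = 29% | 0.9 × 20 + 0.1 × 30 = 21% | 8.0 points |
| Neither, 10% of each arm | 0.9 × 30 + 0.1 × 2 = 27.2% | 0.9 × 20 + 0.1 × 2 = 18.2% | 9.0 points |
| Neither, 20% of the myomectomy arm | 0.8 × 30 + 0.2 × 2 = 24.4% | 20% | 4.4 points |
| Neither, 20% of the UAE arm | 30% | 0.8 × 20 + 0.2 × 2 = 16.4% | 13.6 points |

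So swaps shrink the difference, while women with neither procedure can shrink or enlarge it. In the last row the difference moves away from the null, yet UAE still looks safer than it is: 16.4% instead of 20%.

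**AMH.** If UAE lowers AMH and myomectomy does not (an assumption), a share c of the UAE arm that is not embolised leaves 1 − c of the effect, whether or not those women have a myomectomy. There is also a practical gap: AMH time-points are counted from the procedure, so a woman with no procedure has no defined sampling time.

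**Feasibility.** The procedure received is recorded. The section Confidentiality says that the blood-sample code carries the randomised treatment, so an AMH analysis by receipt needs a planned link to the procedure data.

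**The case against.** The strongest reply is that this is ordinary analysis-plan content. The article is a condensed account, it refers to a fuller plan, and stating intention-to-treat as the principle is neither wrong nor a ban on a labelled supplement. The trial is pragmatic, and its AMH outcome is worded as a comparison of treatment arms. Adverse events also receive a causality assessment and committee scrutiny, so they do not rest on the arm contrast alone. Finally, a comparison by procedure received is open to confounding by the reasons for switching.

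Much of this stands. Intention-to-treat is a legitimate first analysis of every outcome here. A reader might infer that the trial excludes any analysis by receipt. The article does not say that, and the unseen plan may contain one. A reader might also infer that allocation-based analysis always pulls harm towards no difference. The last row of the adverse-event table shows that it need not.

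What remains is the sentence itself. It is a positive, unqualified rule about all analyses, so a by-received analysis of AMH or adverse events would depart from its wording. The words "even after protocol treatment violation" show that such departures were foreseen, though they do not say how often. Confounding is a reason to label and adjust the supplement and to keep it second. It is not a reason to have no estimate of the effect of the procedure.

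**Conclusion.** The point holds in a limited form. The blanket rule suits the quality-of-life outcome and the first analysis of all outcomes. Used alone for AMH and procedure-related adverse events, it can misstate the effect of the procedure. For swaps the direction is known, and the share kept is (1 − c_UAE − c_myo), if swappers respond like the average woman. For women with neither procedure the direction depends on the arm and the outcome.

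The actual size cannot be established, because the documents give no non-receipt rate; the range of 90% to 60% rests on assumed swap rates of 5% to 20% in each arm. It would go too far to say that the trial will give false reassurance about UAE: the article plans no formal conclusion of no harm, and non-receipt may prove rare.

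**What to change.** Keep intention-to-treat for HRQL and as the first analysis of every outcome. Limit the all-analyses sentence to that role, and prespecify for AMH and procedure-related adverse events a supplementary analysis by procedure actually received, as follows:

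- Adjust for the minimisation factors (fibroid size, fibroid number, desire for pregnancy) and age, and for AMH also the baseline value.
- Label the result as not protected by randomisation.
- Report women with neither procedure separately, and state how their AMH time-points are set.
- Present it beside the intention-to-treat result, so that no statement of similar harm rests on the by-allocation estimate alone.

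A complier-average estimate for AMH is optional. Allocation is a single binary instrument, and there are three possible states (UAE, myomectomy, neither), so the effect is not identified without further assumptions. If it is used, state them, including how women with neither procedure are handled.

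The cost is a sentence or two in the protocol or analysis plan, one extra table and a link from the blood samples to the procedure data. No new data on the procedure are needed. The downside is residual confounding by the reasons for switching, which adjustment may not remove and which could bias the supplementary estimate in either direction.

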#### Handling missing data

In the first instance analysis will be completed on received data, with every effort made to follow-up participants (even after protocol treatment violation) to minimise any potential bias. Sensitivity analysis of the primary outcome measure, including imputed values for missing responses, will be performed to determine the robustness of the results obtained. Methods based on multiple imputation will be used.

#### Subgroup analysis

Subgroup analyses are limited by statistical power and can produce spurious results, particularly if numerous analyses are undertaken. For this reason, any subgroup analysis will be limited to the minimisation variables listed in the Initial assessment and randomisation section. Effects within subgroups will only be investigated further if suitable tests for interaction (by including the relevant interaction parameter in the regression model) are statistically robust.

#### Economic evaluation of embolisation compared with myomectomy

An economic evaluation will be conducted alongside the clinical trial to determine the relative cost-effectiveness of UAE compared to myomectomy from the perspective of the NHS and the personal social services [13]. Health utility values associated with each arm of the trial will be calculated from the responses to the EQ-5D questionnaire. Information relating to healthcare resource use associated with the procedures and associated complications and events during the trial period will be collected. Unit costs for all healthcare resource use will be obtained from routinely collected data and the literature to estimate the total costs associated with resource use in each arm of the trial. All costs and quality-adjusted life years (QALYs) will be discounted at the currently recommended rate. Cost-utility analyses will be carried out at two and four years post-randomisation.

Regression analysis will be used to adjust the estimates for relevant covariates, in conformity with the clinical analysis. Cost-effectiveness will be expressed as incremental cost per QALY gained. The 95% confidence limits for the difference in mean costs between arms and for the incremental cost-effectiveness ratios will be calculated using non-parametric bootstrap methods. In addition, the long-term cost-effectiveness of the intervention will be estimated by modelling. A probabilistic decision model will be developed to estimate the subsequent health status and costs beyond the period of the trial until the woman reaches menopause. The model will be populated primarily by data extrapolation from this trial. Extensive sensitivity analyses will be conducted to explore areas of structural uncertainty in the analyses. Parameter uncertainty, including that relating to heterogeneity of the pre-specified subgroups, will be handled by using probabilistic sensitivity analysis and presented using cost-effectiveness curves.

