**Methods:**

After providing informed consent, 216 women with symptomatic fibroids from 43 NHS Hospital Trusts and Health Boards across the United Kingdom will undergo randomisation by a centralised computer system to treatment by either UAE or myomectomy. A minimisation algorithm will be used in order to balance the groups with respect to the following three parameters: the longest dimension of the largest fibroid, the number of fibroids present, and whether the woman currently desires pregnancy.

Using validated questionnaires the women’s quality of life will be compared between groups at six months, one year, two years and four years post-procedure, taking into account pre-procedure scores. An economic evaluation will be conducted alongside the trial to determine the cost-effectiveness of UAE compared with myomectomy.

Validated diaries will also be used to compare menstrual blood loss at the same time-points. The plasma concentration of Anti-Müllerian hormone (AMH), which will act as a proxy measurement of ovarian reserve, will be recorded before the woman has her procedure and then again at six weeks, six months, and twelve months afterwards. Re-intervention rates will be recorded.

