With increasing pressure on ever diminishing NHS budgets the cost-effectiveness is increasing in importance to commissioners and Trusts when deciding which treatment options should be available. The average length of stay in hospital post-hysterectomy is 4.4 days [10], and it is not unusual for women to require an additional three months to recuperate before returning to their normal lives. The average stay in hospital post-myomectomy is 3.6 days and, depending on the route used, the post-procedure recuperation time can be up to several weeks. With its minimally invasive nature, the mean length of hospital stay post-UAE is one day, with a return to normal life typically within a couple of weeks. Whilst superficially this may suggest a significant economic advantage for UAE, the higher re-intervention rates compared with hysterectomy may well negate any cost saving by five years [10].

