### Secondary outcomes

The FEMME trial’s secondary outcomes are:EuroQoL EQ-5D score and visual analogue scale score;Menstrual blood loss, assessed using the Pictorial Blood loss Assessment Chart (PBAC). This is a validated and well-used assessment of menstrual blood loss in women with uterine fibroids;Pregnancy outcomes - pregnancy will be reported by the woman in the first instance. The research nurse or trial coordinator will collect further information with respect to timing of pregnancy, biochemical pregnancy (positive pregnancy test), incidence of miscarriage, outcome of pregnancy, gestational age at delivery or miscarriage, complications of pregnancy, and labour;Adverse events - all adverse outcomes considered to be related to the study protocol or intervention will be collected. Since adverse outcomes may occur many months after intervention, these data will continue to be collected throughout the study;Length of hospital stay;Time to return to work or usual activity;Further treatment for incomplete removal or recurrence of symptoms, including hysterectomies;Ovarian reserve - blood samples will be taken from the women in each treatment arm for the measurement of the plasma levels of Anti-Müllerian hormone (AMH), a compound used as a proxy measurement of ovarian reserve, to determine if there is any difference at six weeks, six months, and twelve months post-procedure.

The time-points at which these follow-ups are performed are shown in Table 1.

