### Randomisation

In order to reduce bias as far as possible, following informed consent but before randomisation, the participant will be given the validated QoL questionnaires (the UFS-QoL and the EuroQoL EQ-5D) and asked to complete them. Once completed and returned to the clinical staff, the patient’s details will be entered onto a centralised online system which will allocate the patient to their treatment (myomectomy or UAE). A minimisation algorithm will be used to ensure that the groups are balanced as evenly as possible with respect to treatment group and also the following variables: the longest dimension of the largest fibroid (under 7 cm or over 7 cm), the number of fibroids present (1 to 3, 4 to 10, over 10), and if the woman desires pregnancy (yes or no).

The number and size of the fibroids present will be determined by imaging with either: magnetic resonance imaging (MRI) (contrast enhanced and/or non-contrast enhanced), ultrasound (vaginal or trans-abdominal), or hysteroscopy.

Should a participant have been randomised on any type of imaging other than MRI then, if local capacity allows, an MRI scan will be requested prior to the patient undergoing their procedure. After randomization, blood will be drawn into two BD Vacutainer® serum separator tubes (SST, BD, [name]) for the proxy measurement of ovarian reserve. These blood samples will be placed into a Royal Mail Safebox™ and sent to Birmingham University’s Human Tissue Repository. Upon receipt, the blood samples will be transformed into serum and stored in a secure biobanking facility at −80°C until analysis. Finally, the participant will be given a copy of the menstrual blood loss diary to take away with them and asked to complete it when they start their next period. Upon completion this blood loss diary will be returned to the trials office in a prepaid envelope provided.

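### EQ-5D is not repeated until six months, so the trial's QALYs cannot register the recovery period after the procedure, in which the protocol says UAE is quicker

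*Protocol article*

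**What the plan says.** The baseline EQ-5D is taken after consent and before allocation: "the participant will be given the validated QoL questionnaires (the UFS-QoL and the EuroQoL EQ-5D) and asked to complete them" (Protocol article, Randomisation). Afterwards, women's "quality of life will be compared between groups at six months, one year, two years and four years post-procedure" (Abstract, Methods). Table 1 agrees. Its UFS-QoL/EQ-5D row is marked before randomisation and at 6 months, 1, 2 and 4 years, and is blank under the columns for discharge and 6 weeks.

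A six-week contact does exist. AMH is sampled "to determine if there is any difference at six weeks, six months, and twelve months post-procedure" (Secondary outcomes), and Table 1 marks fertility potential at 6 weeks.

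The economic section states "Health utility values associated with each arm of the trial will be calculated from the responses to the EQ-5D questionnaire", and "Cost-utility analyses will be carried out at two and four years post-randomisation". Resource use for the procedures is to be collected and costed, and Table 1 records clinical resource use before discharge.

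The section on previous work contrasts the two recoveries. After myomectomy the average stay is 3.6 days and, "depending on the route used, the post-procedure recuperation time can be up to several weeks". After UAE the mean stay is one day, "with a return to normal life typically within a couple of weeks".

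**The concern.** A QALY is the area under a utility curve. Here the curve has no observation between the pre-randomisation score and six months. The protocol's own account puts both recoveries in weeks, well inside that gap, and gives the longer one to myomectomy.

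If women in both arms have recovered by six months, the two arms' curves look alike across the gap, however different the weeks after the procedure were. The cost of the longer stay enters the incremental cost per QALY, but the health loss of the longer recovery does not. A larger sample would not remove this, and no later analysis plan can supply utilities that were never collected.

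**Working it through.** **Inputs from the protocol.** EQ-5D times: baseline, 6 months, 1, 2 and 4 years. Recovery: about two weeks after UAE; a matter of weeks, varying by route, after myomectomy. Women per arm in the power calculation: 86. That figure reproduces: a two-sided t-test at 5% with 90% power for 0.5 SD needs 85.03 per arm, rounded up to 86; 86/0.8 = 107.5, rounded up to 108, gives 216 in total. The protocol states no QALY figure to reproduce.

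**Assumptions (not in the protocol).** Procedure at time 0; a temporary utility loss d of 0.1 to 0.4, equal in both arms; duration 2 weeks after UAE and w = 4 to 8 weeks after myomectomy; equal utility by 6 months; linear interpolation between EQ-5D points.

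**True QALY difference from recovery (myomectomy minus UAE).**

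- Loss fading linearly: −d(w − 2)/(2 × 52). Smallest: 0.1 × 2/104 = 0.0019. Largest: 0.4 × 6/104 = 0.0231.
- Loss constant, then gone: −d(w − 2)/52. Smallest: 0.1 × 2/52 = 0.0038. Largest: 0.4 × 6/52 = 0.0462.

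The overall range is therefore about 0.002 to 0.046 QALY in UAE's favour.

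**What each schedule would capture, for d = 0.3:**

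| Shape, w | True | Planned | Plus 6 weeks | Plus 2 and 6 weeks |
|---|---|---|---|---|
| Linear, 4 | −0.0058 | 0 | 0 | −0.0087 |
| Linear, 6 | −0.0115 | 0 | 0 | −0.0115 |
| Linear, 8 | −0.0173 | 0 | −0.0187 | −0.0303 |
| Constant, 6 | −0.0231 | 0 | 0 | −0.0173 |
| Constant, 8 | −0.0346 | 0 | −0.0750 | −0.0865 |

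Worked row (linear, w = 6): at week 2 the myomectomy loss is 0.3 × (1 − 2/6) = 0.2 and the UAE loss is 0. The area is 0.2 × 2/2 + 0.2 × 4/2 = 0.6 utility-weeks, and 0.6/52 = 0.0115.

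Three things follow. The planned schedule captures zero in every row. A six-week form alone also captures zero whenever recovery is complete by week 6. The two-week form always detects the difference, but not exactly: if a loss remains at week 6, the straight line from there to month 6 overstates it.

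**Scale.** With an assumed two-year QALY SD of 0.2 to 0.4, the standard error of the difference is SD × √(2/86) = 0.030 to 0.061. The omission lies between 0.0019/0.061 = 0.03 and 0.0462/0.0305 = 1.5 standard errors.

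**The case against.** Four counter-arguments deserve weight.

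- **Importance.** A reader might infer that the protocol itself says the arms differ most during recovery. It does not: it says recovery differs and makes no ranking. The largest quality-of-life difference that it quantifies is 12 HRQL points favouring myomectomy at twelve months in the pilot (Sample size). It also reports no difference in improvement at one year in that pilot and no significant difference at five years in an earlier randomised trial. A near-zero QALY increment, whose sign a small omission could decide, is possible but cannot be presumed.
- **Direction.** A reader might infer that the whole cost-utility result is biased against UAE. That goes too far. The protocol reports more re-intervention after UAE, counts hysterectomy as further treatment, and says that three further months of recuperation after hysterectomy are not unusual. Those recoveries can also fall between time-points, which would favour UAE. As an illustration on assumed figures, a loss of 0.2 for 13 weeks is 0.2 × 13/52 = 0.05 QALY. A 10 to 20 percentage-point excess of hysterectomy after UAE would make that 0.005 to 0.010 per woman, against 0.0115 in the linear six-week case above. This objection stands.
- **Size.** The protocol's wording on myomectomy recuperation is an upper limit that depends on route, and laparoscopic and hysteroscopic routes are allowed. Applying a long recovery to every woman overstates the mean. This stands, and the low end of the range is negligible.
- **Method.** The article does not state an interpolation rule, and it promises extensive sensitivity analyses. The fuller economic plan may give the rule. But no rule creates observations in the gap, and a decrement imposed in sensitivity analysis is an assumption rather than trial data. Length of stay and time back to usual activity are collected, but they are not utilities, and the economic section does not say that they will be used as such.

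**Conclusion.** The point holds in limited form. The trial's observed QALYs cannot register a recovery loss that has resolved by six months, although the protocol describes a difference between the arms in that period and costs the inpatient part of it. For the index procedure the omission understates UAE's early benefit by roughly 0.002 to 0.046 QALY per woman, from negligible to about 1.5 standard errors on the assumed SDs. The direction for the index procedure assumes that the loss after myomectomy is at least as deep as that after UAE and lasts longer. That both groups have recovered by six months is inferred from the protocol's description, not stated in it. The net bias at two and four years cannot be signed from the document. The clinical primary outcome at two years is not touched.

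**What to change.** For women still to be treated:

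- Add a short take-home EQ-5D at about two weeks after the procedure. This is the essential part, because a six-week form alone records nothing if recovery is over by then.
- Add EQ-5D to the 6-week column of Table 1, at the contact where AMH is already sampled.
- Use both scores in the QALY calculation, and state how a loss still present at week 6 is carried towards month 6, since a straight line can overstate it.

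For women already past those times, pre-specify a sensitivity analysis that applies a recovery decrement over a range of depths and durations. Length of stay and time to return to usual activity could inform it.

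The cost is one brief questionnaire to take home, one more at an existing contact, an edit to Table 1 and a protocol amendment, whose class is for the sponsor and ethics committee to decide. The downsides are slightly more questionnaire burden and early data for later recruits only. The article reports the trial as still recruiting, so the change was open when it was published.

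### Bootstrap confidence limits are fixed for the ICER with no provision for a QALY difference not clearly away from zero, where such limits may be uninterpretable

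*Protocol article*

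**What the plan says.** All of the planned economic analysis is in the Protocol article, section Economic evaluation of embolisation compared with myomectomy.

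- Summary measure: "Cost-effectiveness will be expressed as incremental cost per QALY gained".
- Timing: "Cost-utility analyses will be carried out at two and four years post-randomisation".
- Uncertainty in the trial-based result: 95% limits for the difference in mean costs and also "for the incremental cost-effectiveness ratios will be calculated using non-parametric bootstrap methods".
- After the description of a long-term decision model, parameter uncertainty "will be handled by using probabilistic sensitivity analysis and presented using cost-effectiveness curves".

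The section gives no expected QALY or cost difference, no willingness-to-pay threshold, and no rule for a QALY difference that may be zero.

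The section Previous work comparing UAE with myomectomy reports that in an earlier randomised trial "there were no significant differences in the reported QoL between the groups at five years". On cost, it says of the higher re-intervention rate after UAE: "This negated the initial cost benefit of UAE over surgery at 12 months and made both treatments cost-neutral at five years". It also says that the pilot found no difference in QoL improvement at one year.

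**The concern.** A ratio does not identify a position on the cost-effectiveness plane. A negative ICER can mean that UAE is cheaper and better, or dearer and worse. A positive one can mean a gain at extra cost, or a loss with a saving. While nearly all replicates lie in one quadrant, sorting the ratios orders them sensibly. Once the QALY difference changes sign across replicates, sorting mixes opposite conclusions, and values near the break go to plus or minus infinity. The two limits then do not enclose a set of compatible results.

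At stake is the uncertainty statement attached to the economic result. The article's background presents cost-effectiveness as increasingly important to commissioners. A reader given limits such as minus £92,000 to plus £118,000 per QALY could not tell which treatment they favour. If the plan provides no other measure, the replacement would be chosen after the quadrant is known.

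**Working it through.** **The plan's own figures.** The article states no figure for the ICER or its interval, so there is none to reproduce. The input taken from it is the evaluable sample size in the section Sample size: 86 per group. For 0.5 SD, 90% power and two-sided 5%, the normal formula gives 85 per arm; the t-test version gives 85.03, rounded up to 86. This agrees with the article.

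**Assumed inputs.** The documents give none of these: QALY SD per woman 0.3 (range 0.2 to 0.5), cost SD £2,000, cost–QALY correlation −0.1, true QALY difference d from 0 to 0.15, true cost difference £0 to £1,000.

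**Step 1. Precision of the QALY difference.** SE = SD × √(2/n) = 0.3 × √(2/86) = 0.046. The observed difference must exceed 1.96 × 0.046 = 0.09 QALY for its 95% interval to exclude zero (0.06 at SD 0.2, 0.15 at SD 0.5).

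**Step 2. How often the interval includes zero.** Probability = Φ(1.96 − d/SE) − Φ(−1.96 − d/SE). At SD 0.3 and d = 0.10, d/SE = 2.19, so the probability is 0.41.

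| True QALY difference | SD 0.2 | SD 0.3 | SD 0.5 |
|---|---|---|---|
| 0.05 | 63% | 81% | 90% |
| 0.10 | 9% | 41% | 74% |
| 0.15 | 0.2% | 9% | 50% |

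With 108 per arm (all 216 women) and SD 0.3 the figures at 0.05 and 0.10 are 77% and 31%.

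**Step 3. What happens to the ICER limits.** Percentile bootstrap, 86 per arm, 5,000 replicates, QALY SD 0.3, with the observed differences set to the values shown:

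| QALY and cost difference | Replicates with negative QALY difference | 2.5% and 97.5% points of the ratio, per QALY |
|---|---|---|
| 0 and £0 | 50% | about −£89,000 and £77,000 |
| 0.05 and £500 | 14% | about −£92,000 and £118,000 |
| 0.15 and £1,000 | 0.2% | about £2,200 and £22,900 |

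In the first row the four quadrants hold 20%, 29%, 29% and 21% of replicates, so the limits have no ordered meaning. In the last row 99.8% lie in one quadrant and the interval can be read in the usual way.

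**Step 4. The same case as net benefit.** NMB = λ × ΔQALY − Δcost. At an assumed λ of £20,000 per QALY its SE is √{(2/86) × [(20,000 × 0.3)² + 2,000² + 2 × 0.1 × 20,000 × 0.3 × 2,000]} = √{(2/86) × 42.4 million} = £993. For 0.05 QALY and £500, NMB = £1,000 − £500 = £500, with 95% limits 500 ± 1.96 × 993, about −£1,450 to £2,450. That interval has one meaning whichever quadrants the replicates occupy.

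**Step 5. Coverage.** With assumed SEs of 0.05 QALY and £250 and a true cost difference of £300, simulated coverage of the nominal 95% ICER limits is about 87%, 94% and 98% at true differences of 0.01, 0.02 and 0.05 QALY. Undercoverage is clear only at the smallest of these. The main problem is interpretation.

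**The case against.** A reader might infer that near-zero differences are expected and that the interval is therefore bound to fail. The documents do not support this. No section states an expected QALY or cost difference. A non-significant QoL result, on the SF-36 in one earlier trial, is not a zero difference. Cost-neutrality was reported at five years, UAE had a cost advantage at 12 months, and the analyses here are at two and four years. The background also gives hospital stays of 1 day after UAE and 3.6 days after myomectomy. The section Sample size reports a 12-point pilot difference favouring myomectomy and powers the trial for 0.5 SD. All of this stands against a prediction of failure. The power argument is limited, though: it concerns the disease-specific UFS-QoL score, whereas QALYs come from the EQ-5D, for which the article gives no power calculation.

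Three further objections:

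- The article says non-parametric bootstrap without naming percentile limits, so the figures above assume that version. This stands in part. Other bootstrap limits that order values of the ratio share the sign ambiguity, and no special handling is mentioned.
- Cost-effectiveness curves are planned, and these remain valid across quadrants. They follow the decision-model sentences and are tied to parameter uncertainty. The text does not rule out within-trial curves, but does not clearly provide them.
- Net benefit and thresholds are details that a condensed article may leave to a fuller document. That is fair, and their absence alone would not be a point. The point is the method that the article does fix.

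**Conclusion.** The concern holds in conditional form. The article commits to confidence limits on a ratio and makes no provision for a QALY difference that is not clearly different from zero. In that case the limits may be uninterpretable. Under the central assumptions (86 per arm, QALY SD 0.3) the chance of being in that position is about 81% at a true 0.05 QALY, 41% at 0.10 and 9% at 0.15. It moves considerably with the assumed SD: at 0.10 QALY it runs from 9% to 74%. The earlier trial and the pilot, as described in the background, make a small difference plausible, and no more than that. If the difference is large, the planned limits will be readable.

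The size of the point is minor. It affects the reporting of a secondary economic analysis. The primary outcome, its analysis and the sample size are untouched.

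**What to change.** For the trial-based analyses at two and four years:

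- Replace the confidence limits for the ICER with incremental net monetary benefit and its bootstrap 95% interval at prespecified willingness-to-pay thresholds. The article states none, so they must be named before the data are seen.
- Use the regression adjustment already planned in the economic section.
- Plot the same replicates on the cost-effectiveness plane and add an acceptability curve for the within-trial result, separate from the curves for the decision model.
- Report the ICER as a point estimate. Keep the bootstrap limits for the cost difference.

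The cost is about one sentence in the plan, the choice of thresholds and slightly longer output. The same bootstrap replicates serve, and no extra data are needed.
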